# The Early Detection and Case Management of Skin Diseases With an mHealth App (eSkinHealth): Protocol for a Mixed Methods Pilot Study in Côte d’Ivoire

**DOI:** 10.2196/39867

**Published:** 2022-09-21

**Keywords:** skin diseases, neglected diseases, skin NTDs, teledermatology, telemedicine, remote consultation

## Abstract

**Background:**

There is a high prevalence of skin diseases sub-Saharan Africa, including skin neglected tropical diseases (NTDs) that could lead to lifelong disabilities and deformities if not diagnosed and treated early. To achieve early detection and early treatment of these skin diseases, we developed a mobile health app, eSkinHealth.

**Objective:**

This paper outlines a protocol for evaluating the effect of our eSkinHealth app in the early detection and effective management of skin diseases in Côte d’Ivoire.

**Methods:**

A mixed methods pilot trial will be conducted in Côte d’Ivoire and will consist of 3 phases: (1) the development and improvement of the eSkinHealth app, (2) a pilot trial to evaluate the usability of the eSkinHealth app for local medical staff in Côte d’Ivoire, and (3) a pilot trial to evaluate the effectiveness of early detection and case management of targeted skin NTDs (Buruli ulcer, leprosy, yaws, and lymphatic filariasis) with the eSkinHealth app in Côte d’Ivoire. The pilot study will be implemented as a 2-arm trial with local health care providers and patients with skin NTDs over a 3-month follow-up period. The local health care providers will be assigned to an intervention group receiving the eSkinHealth app to be used in their daily practices or a control group. Training will be provided on the use and implementation of the app and the diagnostic pipeline to the intervention group only, while both groups will receive training on skin diseases. Our primary outcome is to evaluate the early detection and effective management of skin diseases using the eSkinHealth app in Côte d’Ivoire by the number of cases diagnosed and managed. Additionally, we will evaluate the eSkinHealth app with validated questionnaires and in-depth interviews. Procedures of our methods have been reviewed and approved by the Institutional Review Board of the Ministry of Health, Côte d’Ivoire and by Tulane University in 2021.

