## Methods

### Study Design

A mixed methods pilot trial will be conducted in Côte d’Ivoire where there is coendemicity with multiple skin NTDs, including Buruli ulcer, leprosy, yaws, scabies, and lymphatic filariasis. The trial will consist of 3 phases: (1) development and improvement of the eSkinHealth app and the platform, (2) pilot trial to evaluate the usability of the eSkinHealth app, and (3) pilot trial to evaluate the effectiveness of early detection and case management of skin diseases with the eSkinHealth app. Phases 2 and 3 of the study will be implemented as a 2-arm trial over a 3-month follow-up.

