### Participant Inclusion/Exclusion Criteria

Eligible patients will be defined as those who are clinically suspected of or diagnosed with skin NTDs (Buruli ulcer, leprosy, yaws, scabies, and lymphatic filariasis) or suspected of other clinically diagnosed skin conditions, with fewer than three concomitantly identified skin conditions, and able to consent for themselves. Ineligible patients have more than three skin conditions and reside outside of the target site.

Local health care providers (ie, doctors, nurses, or community health workers/volunteers) must meet all eligibility requirements to enroll in the study. Eligible local health care providers are 18 years or older, working at primary health centers or clinics (PHCs) or within the catchment area of the selected PHCs in Côte d’Ivoire, able to read and speak fluent French, willing to participate in the pilot study for the 3-month study duration and use a provided tablet with the eSkinHealth app if they were assigned in the intervention group, and able to consent for oneself. Ineligible local health care providers will be defined as those who are planning to leave the job at the PHCs within the study period and have difficulty operating mobile devices.

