#### Phase 3: Pilot Trial to Evaluate the Effectiveness of eSkinHealth for Early Diagnosis and Case Management

The same local health care providers as in phase 2 will participate. They will register patients suspected of the targeted skin NTDs (Buruli ulcer, leprosy, yaws, scabies, and lymphatic filariasis) who provide an informed consent during active case finding and during consultation at PHC throughout the trial period on the eSkinHealth app platform. Clinical data at the time of initial identification and at every follow-up visit until cure will be entered in eSkinHealth, including the photos of their skin lesions. The data will be uploaded when connected to the internet and integrated into one database server. When in need of a consultation, a request will be sent to remote experts/dermatologists in Côte d’Ivoire or members of the global health dermatology community, and advice or a clinical confirmation will be provided. As for the control arm, they will diagnose and manage the cases with skin NTDs as usual following the national standard guidelines. Reporting cases from the control arm will be done by paper-based reports using the consultation registry of the Ministry of Health and the skin NTD reporting forms of the World Health Organization [25].

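### The primary case count covers skin diseases in one place and skin NTDs in another, and the targeted NTD list does not consistently include scabies

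*Protocol article*

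**What the plan says.** All references are to the protocol article.

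**Which cases the primary outcome counts**
- Abstract, Methods: the primary outcome is "early detection and effective management of skin diseases using the eSkinHealth app", measured by the number of cases diagnosed and managed.
- Discussion: the primary assessment is the number of skin NTD cases diagnosed and managed.
- Outcome Measurement and Data Analysis: both refer to numbers diagnosed and early detection, and neither says of which diseases.

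**What phase 3 targets**
- Abstract, Methods: "targeted skin NTDs (Buruli ulcer, leprosy, yaws, and lymphatic filariasis) with the eSkinHealth app", four diseases.
- Phase 3 section: "targeted skin NTDs (Buruli ulcer, leprosy, yaws, scabies, and lymphatic filariasis", five diseases.
- Study Design: the setting has "multiple skin NTDs, including Buruli ulcer, leprosy, yaws, scabies, and lymphatic filariasis", again five, but phase 3 itself is described as "early detection and case management of skin diseases with the eSkinHealth app".

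**Who may enter**
- Participant Inclusion/Exclusion Criteria: patients suspected of or "diagnosed with skin NTDs (Buruli ulcer, leprosy, yaws, scabies, and lymphatic filariasis", "or suspected of other clinically diagnosed skin conditions".
- Recruitment Procedure: people with skin diseases, with no restriction to NTDs.
- Phase 3 section: providers register "patients suspected of the targeted skin NTDs (Buruli ulcer, leprosy, yaws, scabies, and lymphatic filariasis".

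**The concern.** The primary outcome is a number of cases, so the set of diseases is part of its definition. If that set is not fixed, whoever analyses the trial can choose it once the counts by disease are known.

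Two features of the article make the choice matter. First, the conditions that move in or out of the count may be frequent ones. The Introduction uses scabies as its example of a very common skin disease and cites skin disease prevalence in children of 23.3% to 80.4%. It names leprosy, Buruli ulcer and lymphatic filariasis separately as causes of lifelong disability. A change in the disabling NTDs could be diluted by common conditions, or a change in a common condition could be read as an effect on the disabling NTDs.

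Second, the arms do not record cases in the same way. Phase 1 describes the app as suited to a wide range of skin conditions. According to the Phase 3 section, the control arm reports on paper, through the Ministry of Health consultation registry and the World Health Organization skin NTD forms. A broad count could therefore partly reflect which instrument captures non-NTD conditions.

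**Working it through.** **No plan figure to reproduce.** Sample Size Estimation gives 1320 patients as a convenience sample, without a calculation and without any expected count or share by disease. The only powered figure, 44 providers, does not bear on this point.

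**Step 1: apply each wording to the same patient.**

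| Patient | Skin diseases (Abstract outcome) | Skin NTDs, five-disease list | Skin NTDs, four-disease list |
|---|---|---|---|
| Leprosy | counted | counted | counted |
| Scabies | counted | counted | not counted |
| Eligible condition outside the five NTDs | counted | not counted | not counted |

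The first column and the other two come from differing statements of the primary outcome. The split between the last two columns comes from the description of the phase 3 target, not from an outcome statement. Outcome Measurement and Data Analysis, where one would look for the answer, do not settle either question.

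**Step 2: how far the count could move (assumed shares).** Take all 1320 patients as counted cases, and assume 30% have one of the five NTDs and 20% to 80% of those have scabies.
- Any skin disease: 1320.
- Five NTDs: 1320 × 0.30 = 396.
- Four NTDs: 396 × 0.80 = 317, down to 396 × 0.20 = 79.

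**Step 3: how far the between-arm ratio could move (assumed effects).** Suppose the arms would have equal case loads without the app, the app doubles detection of the four NTDs, and other conditions are unaffected. Let s be the unaffected share of **control-arm** cases.
- Ratio = 2(1 − s) + s = 2 − s.
- s = 0.5 gives 1.5; s = 0.8 gives 1.2.

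The definition of s matters. If s is instead the share pooled over both arms, with control-arm four-NTD count a and unaffected count u in each arm, then s = 2u/(3a + 2u).
- s = 0.5: u = 1.5a, ratio = (2a + 1.5a)/(a + 1.5a) = 1.4.
- s = 0.8: u = 6a, ratio = (2a + 6a)/(a + 6a) = 8/7 = 1.14.

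In the other direction, suppose only scabies doubles and scabies alone makes up 80% of control-arm cases. The ratio is then 0.2 + 2 × 0.8 = 1.8, with no change in the four NTDs. If part of that 80% is other, unaffected conditions, the ratio is lower.

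**The case against.** The strongest reply is that this is loose wording in a condensed article. Every disease list in the body of the Methods has five entries, including the Phase 3 section, and the four-disease list occurs once, in the Abstract. The simplest reading is that scabies was left out there by mistake. The app is not disease-specific, so broad eligibility with a narrower outcome is a legitimate design, and a statistical analysis plan that is not shown may fix the count.

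Much of this stands, and it rules out two stronger readings.
- A reader might infer three competing primary outcomes. The outcome statements name only two sets, skin diseases and skin NTDs, or none. The four-disease list is never attached to an outcome; it only leaves open what skin NTDs means.
- A reader might infer that the eligibility criteria contradict the Phase 3 section. The Phase 3 section says whom providers register but does not say that no one else is registered, so the two can coexist.

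The reply does not remove the conflict between the Abstract and the Discussion over the primary count. That is a disagreement between two current statements, not a detail left to another document. Nor does the article say that a narrower outcome within a broader population is intended.

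**Conclusion.** The point holds as an internal inconsistency in the definition of the primary count. The main ambiguity is all skin diseases against skin NTDs; the secondary one is whether scabies belongs to the targeted NTDs. It should be corrected even in a pilot, because the Discussion presents the results as robust evidence for policy makers.

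The size of the consequence cannot be derived from the article. The counts and ratios in the working rest on assumed shares and effects, and they show only that the choice of set can matter. It would be tempting to read 1.5 or 1.2 as an estimate of distortion in this trial, but the article gives no disease-specific figures to support that. Likewise, the different recording instruments make a recording difference between the arms possible; the article does not show that one will occur.

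**What to change.** Before the arms are compared:
- Define the primary count, in the Abstract, Outcome Measurement, Data Analysis and Discussion, as cases of the five NTDs listed in Study Design, the eligibility criteria and the Phase 3 section, applied identically in both arms.
- Add scabies to the list in the Abstract.
- Count other skin conditions as a secondary outcome, and show the count by disease so that scabies can be seen apart from the other four.
- Leave the eligibility criteria as they are, and add a sentence saying which eligible patients enter the primary count. Narrowing eligibility would change the population after enrolment began in February 2022, and would remove the patients needed for the secondary outcome.

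The cost is wording and one table by disease, with no new data, provided that diagnosis is recorded for each case in both arms. That should be confirmed for the paper reports of the control arm.

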**Results:**

This study was funded in 2021. We started the enrollment of patients in February 2022, and data collection is currently underway. We expect the first results to be submitted for publication in 2023.

**Conclusions:**

Our eSkinHealth app is a field-adapted platform that could provide both direct diagnostic and management assistance to health workers in remote settings. The study will provide evidence for the usability and the effectiveness of the eSkinHealth app to improve the early detection and case management of skin NTDs in Côte d’Ivoire and, furthermore, is expected to contribute to knowledge on mobile health approaches in the control of skin NTDs.

**Trial Registration:**

ClinicalTrials.gov NCT05300399; https://clinicaltrials.gov/ct2/show/study/NCT05300399

**International Registered Report Identifier (IRRID):**

DERR1-10.2196/39867

## Introduction

The prevalence of skin diseases is high in sub-Saharan Africa, particularly in children, and the reported prevalence ranges from 23.3% to as high as 80.4% in this age group [1-7]. These diseases are most often overlooked due to a lack of local specialists and lack of experience among Western specialists looking at darker skin [8]. However, if left untreated, even some of the most common skin diseases could have severe complications (eg, scabies could lead to rheumatic fever and nephropathy, as well as often debilitating physical, social, and mental effects that may deprive one of educational and social opportunities [9,10]). Furthermore, some diseases, including leprosy, Buruli ulcer, lymphatic filariasis, and other skin infections, lead to lifelong disabilities and deformities if not diagnosed and treated early [9,11]. These skin infections that prevail in low- and middle-income countries (LMICs) are members of the skin neglected tropical diseases (NTDs) listed by the World Health Organization and targeted for disease control globally.

Observation of the skin could be very informative. Without undergoing invasive examinations requiring special skills and equipment, many skin diseases could be diagnosed with just sufficient patient history and observation of the skin. This is well suited to field settings in LMICs. Photos of the skin lesions could serve as an alternative to direct observation and, if of sufficiently good quality, could allow for the diagnosis to be made on-site or remotely. Telemedicine for dermatology, or teledermatology, is currently an emerging field taking advantage of this unique feature of skin diseases. A few attempts of teledermatology have been made in sub-Saharan African countries and have shown promising results [12-14]. These previous efforts have faced a number of challenges that we plan to overcome with the proposed work with the following features:

A field-adapted mobile health (mHealth) app that could provide direct diagnostic and management assistance to health care workers in a remote setting: There is no novel tool to support teledermatology, especially in LMICs where internet accessibility and connection quality is a challenge. It is also of note that photos alone are often not adequate to make a correct diagnosis as outlined previously by Resneck et al [15]. Although clinical photos offer essential information, they need to be accompanied by some clinical information to make a more accurate diagnosis. Furthermore, such a tool needs to be optimized for use in the skin of people of color, given that diagnosis of several skin conditions on skin type IV and darker remains a challenge [16].A platform for storage of longitudinal patient records for improved follow-up: We have been conducting active surveillance for skin diseases in Cote d’Ivoire [1]. After providing a diagnosis, follow-up should be performed with the patient, especially as most of the skin diseases are chronic in nature; this is an ethical obligation in medicine. However, there is a lack of skills and expertise in dermatology to pursue this, which is a universal situation in most LMICs [17]. Our field is no exception, and it has been challenging to follow-up with our patients without making repeated field visits, which are often a long distance from city centers [18]. In addition, this lack of capability to follow up with patients is partly due to the lack of a system to document patient records. A platform that stores serial photo documentation of the clinical course could guide health care practitioners, both on-site and remotely, to provide better care.A platform for formal collection and automatic organization of clinical and image data of the skin: Currently, teledermatology is mostly done in platforms without any formal framework for the collection or organization of data [19], and there is a need for developing such a platform both for direct patient care and epidemiologic purposes, especially for the organization of clinical photos, which is a cumbersome task if done manually. Patient information management is another challenge in developing a successful teledermatology system, ensuring that patient privacy is fully protected. Nowadays, social networking sites such as WhatsApp and Facebook are sometimes used for teledermatology [20,21], but these informal platforms need to be used with care considering patient privacy. If there is a platform that addresses these gaps, this could further support data analysis and quality control.

In summary, with targeted training, a technology-assisted decision support system, and a telemedicine network, local health care workers could be leveraged to enhance the diagnosis and management of these conditions as well as support health care managers in quality control. If an mHealth app that overcomes these current gaps and weaknesses is developed, this could serve as a breakthrough to managing skin diseases in LMICs.

This project is built upon a previous project for the development of a prototype smartphone/tablet app for skin diseases, which we named eSkinHealth. This app is aimed at on-site and remote diagnosis, monitoring, clinical decision support, and geographic mapping of skin diseases, including skin NTDs adapted for use in LMICs and for skin type IV and darker. Through this project, we will develop a powerful and comprehensive but easy-to-use mHealth app that could be used for the diagnosis and management of all types of skin conditions, especially focused for use in LMICs and for skin type IV and darker.

## Methods

### Study Design

A mixed methods pilot trial will be conducted in Côte d’Ivoire where there is coendemicity with multiple skin NTDs, including Buruli ulcer, leprosy, yaws, scabies, and lymphatic filariasis. The trial will consist of 3 phases: (1) development and improvement of the eSkinHealth app and the platform, (2) pilot trial to evaluate the usability of the eSkinHealth app, and (3) pilot trial to evaluate the effectiveness of early detection and case management of skin diseases with the eSkinHealth app. Phases 2 and 3 of the study will be implemented as a 2-arm trial over a 3-month follow-up.

### Participant Inclusion/Exclusion Criteria

Eligible patients will be defined as those who are clinically suspected of or diagnosed with skin NTDs (Buruli ulcer, leprosy, yaws, scabies, and lymphatic filariasis) or suspected of other clinically diagnosed skin conditions, with fewer than three concomitantly identified skin conditions, and able to consent for themselves. Ineligible patients have more than three skin conditions and reside outside of the target site.

Local health care providers (ie, doctors, nurses, or community health workers/volunteers) must meet all eligibility requirements to enroll in the study. Eligible local health care providers are 18 years or older, working at primary health centers or clinics (PHCs) or within the catchment area of the selected PHCs in Côte d’Ivoire, able to read and speak fluent French, willing to participate in the pilot study for the 3-month study duration and use a provided tablet with the eSkinHealth app if they were assigned in the intervention group, and able to consent for oneself. Ineligible local health care providers will be defined as those who are planning to leave the job at the PHCs within the study period and have difficulty operating mobile devices.

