### Recruitment Procedure

We will select 10 to 12 PHCs in health districts with multiple skin NTDs coendemicity as our study site and allocate them equally into intervention and control arms. Targeted patients will include individuals with skin diseases identified through skin surveillance activities and who access the selected PHCs for diagnosis and treatment of their conditions. Local health care providers will be recruited purposively from our study site. A total of 44 local health care providers, including nurses and community health workers, will be selected to participate in the study; the number per PHC will be based on the population of the catchment area of the PHC. All participants will be enrolled formally only after signing the informed consent form.

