### Intervention

#### Phase 1: Development and Improvement of the eSkinHealth App and the Platform

The current prototype of the eSkinHealth app is made up of six primary functions, which include (1) patient ID and demographics, (2) symptom list, (3) symptom basic information, (4) history list, (5) record of the day, and (6) photo list (Figure 1). The content of these screens has been developed based on our previous field surveys [1] and from the research team’s experience in managing dermatological patients. We have built-in some special features within each screen (Figure 2). The screen with the patient ID and demographics allows for entry of basic information, automatic calculation of BMI, and assessment of the patients’ nutritional status. The nutritional status could be an important risk factor/indicator for several skin conditions, including wound healing. Patients may present with multiple skin conditions, and this could be organized and managed under the screen of the symptom list. In the screen with the symptom basic information, important information on diagnosing a skin disease is provided as a drop-down choice, so it is not missed and easy to enter. If patients are to return to the clinic, the evolution of their symptom could be seen at a glance in the screen with the history list, allowing comparison with previous symptoms. Lastly, physical examination results of a 1-day visit could be entered in the screen with the record of the day, and clinical photos could be taken, which will be automatically organized in the screen with the photo list. A unique function that we included in our tool is the itchiness and pain visual scale whereby patients themselves could touch the screen and indicate how they are experiencing these sensations each time.

This app is not a disease-specific tool and is fit for use for a wide range of skin conditions with two algorithms: one for nonulcerative skin diseases and another for wounds, a very common manifestation of the skin in LMICs but with different follow-up approaches as compared to other skin conditions. Other special features of the app include patient information security using QR codes. Patients are issued a QR code at their first visit. When they present it to a local health care provider with a device running the eSkinHealth app during follow-up visits, it allows access to their records, making their health records secure and portable.

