### Outcome Measurement

For phase 2, we will use a validated questionnaire (SUS). The outcome measurement is an average of the SUS score. Bangor et al [26] found that the SUS was highly reliable (α=.91) and useful over a wide range of interface types [27,28]. The SUS consists of 10 statements with responses in the form of a 5-point Likert scale (eg, 1: strongly disagree; 5: strongly agree). According to Bangor et al [27], a SUS score above 68 would be considered above average. In addition, a SUS score above an 80 is considered excellent and places the product in the top 10% of products tested [29]. We will use the French language version of the SUS. We will assess the usability at baseline, the midpoint (6 weeks), and the end of the study (12 weeks). In-depth interviews will be performed at the end of the study.

For phase 3, differences in case numbers diagnosed and the early detection and follow-up between the intervention group (diagnosis with the app) and the control group (usual diagnosis) will be measured as the primary outcome of this study.

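### The cap on identified skin conditions rests on something the app may change, so if it governs the primary case count it can exclude patients unequally by arm

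*Protocol article*

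**What the plan says.** All references are to the protocol article.

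- **Participant Inclusion/Exclusion Criteria.** Eligible patients are those "with fewer than three concomitantly identified skin conditions" who can give their own consent. The exclusion sentence uses a different threshold: "Ineligible patients have more than three skin conditions and reside outside of the target site". Exactly three conditions falls under neither sentence.
- **Recruitment Procedure.** The plan is to select 10 to 12 health centres and "allocate them equally into intervention and control arms". The arm is therefore fixed before any patient is assessed. Formal enrolment follows signed consent.
- **Phase 3.** In the app arm, providers register consenting patients suspected of a targeted skin NTD on the platform and enter data and photos from first identification. When they need help, "a request will be sent to remote experts/dermatologists in Côte d’Ivoire or members of the global health dermatology community". Control providers diagnose as usual and report on paper registers and forms. The cap is not repeated here.
- **Outcome Measurement.** The phase 3 primary outcome is "differences in case numbers diagnosed and the early detection and follow-up between the intervention group" and the control group.
- **Sample Size Estimation.** The 1320 patients are described as a convenience sample of people eligible for the study.

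**The concern.** The criterion counts conditions identified, not conditions present, so it depends on the examination. The examination differs by arm. The app arm has a symptom list that can hold several conditions, drop-down fields, organised photos and access to remote experts; the control arm has usual consultation. Because allocation comes first, eligibility can respond to the intervention.

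Take two patients with the same three conditions, one of them a targeted NTD. If the control provider records two, that patient is eligible. If the app provider records all three, that patient fails the inclusion sentence. Where the primary count includes only eligible patients, thorough examination then costs the app arm a case. At stake are the comparability of the patients counted in each arm and the loss of true NTD cases from an outcome meant to measure detection.

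**Working it through.** The article states no figure for this point, so there is nothing to reproduce. Both calculations below are illustrations on assumed inputs. Neither separates targeted NTDs from other skin conditions.

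**1. Effect of the cap alone, with no true difference in cases**

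Assumptions: every counted patient has one identified condition plus a Poisson number of extra identified conditions with mean m. The app doubles m. The cap applies to the count in both arms.

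- Excluded at three or more conditions (two or more extras): 1 − e^(−m)(1 + m)
- Excluded only at more than three (three or more extras): 1 − e^(−m)(1 + m + m²/2)
- App/control ratio = share retained with app ÷ share retained in control

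| m, control / app | Cut | Excluded, control | Excluded, app | Ratio |
|---|---|---|---|---|
| 0.2 / 0.4 | three or more | 1.75% | 6.16% | 0.9384/0.9825 = 0.955 |
| 0.3 / 0.6 | three or more | 3.69% | 12.19% | 0.8781/0.9631 = 0.912 |
| 0.2 / 0.4 | more than three | 0.1% | 0.8% | 0.993 |
| 0.3 / 0.6 | more than three | 0.4% | 2.3% | 0.980 |

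The two thresholds in the eligibility section thus give a spurious deficit of about 4% to 9% or of 0.7% to 2.0%.

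**2. Allowing the app to find more patients as well**

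Assumptions: true conditions per person are Poisson with mean μ. Each is detected independently with probability 0.5 in control and 0.8 with the app. Without a cap, a patient counts if at least one condition is detected; with the cap, if one or two are.

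With λ = μ × detection probability, the counted share is proportional to 1 − e^(−λ) without the cap and to e^(−λ)(λ + λ²/2) with it. For μ = 1 the capped ratio is e^(−0.8)(0.8 + 0.32) ÷ e^(−0.5)(0.5 + 0.125) = 0.503/0.379 = 1.328. The uncapped ratio is 0.551/0.393 = 1.400.

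| μ | Affected people with three or more conditions | Removed by cap, control | Removed by cap, app | Ratio without cap | Ratio with cap |
|---|---|---|---|---|---|
| 0.2 | 0.6% | 0.2% | 0.4% | 1.554 | 1.550 |
| 0.5 | 3.7% | 1.0% | 2.4% | 1.490 | 1.469 |
| 1.0 | 12.7% | 3.7% | 8.6% | 1.400 | 1.328 |
| 2.0 | 37.4% | 12.7% | 27.1% | 1.263 | 1.054 |
| 3.0 | 60.7% | 24.6% | 47.3% | 1.170 | 0.818 |

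In every row the cap removes a larger share in the app arm and lowers the ratio. The loss is negligible in the first row and about 1% in the second. The ratio falls below 1 only in the last row, where most affected people have three or more conditions.

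**The case against.** The strongest reply is that the article never says the primary count is limited by the cap. Outcome Measurement refers to cases diagnosed, Phase 3 does not repeat the cap, and control cases come from routine registers. This stands as a limit on the claim. The sample size section makes restriction to eligible patients a natural reading, but no more than that.

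A reader might infer that app-arm patients are dropped once a third condition is found. The article does not support this: it states no rule for removing enrolled patients and does not fix when conditions are counted. Remote advice is sought on request and draws on data already entered, so it may come too late to affect eligibility. What remains is the examination at first contact, when the app is already in use.

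A reader might also infer that the cap contradicts the app's purpose, since the Phase 1 section says "Patients may present with multiple skin conditions, and this could be organized and managed under the screen of the symptom list". It does not. Two conditions are allowed and are already multiple, and an app may do more than a pilot's eligibility rules require.

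Three further points limit the weight. Better detection also adds patients who would otherwise have no diagnosis, so the net effect on the app arm's count can be positive. Both arms are trained in screening, and nothing in the article supports a doubling of extra findings. Any bias runs against the app, so it would not create a false benefit.

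None of this removes the structural fault. The rule depends on a post-allocation quantity that the intervention may raise and that lies close to the outcome.

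**Conclusion.** The point holds as a conditional one. Eligibility depends on how many conditions an unblinded provider identifies after allocation. If the case count is confined to eligible patients, the cap can exclude a larger share in the app arm and tends to pull the app/control ratio down. That the app arm will lose patients is not established.

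The size cannot be fixed from the article. It depends on three unknowns: how common multiple conditions are, how much the app changes the number identified, and which threshold applies. Under the assumed Poisson means, the ratio with no true difference is 0.91 to 0.96 with the stricter cut and 0.98 to 0.99 with the looser one. Where three or more conditions are rare, the effect can be ignored. The change is still worth making, because it removes a possible bias at little cost.

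**What to change.** For the primary case count, state that every consenting patient with a targeted skin NTD is counted in both arms, whatever number of other skin conditions is identified. This also makes the conflicting thresholds irrelevant to the primary outcome.

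If a cap is wanted for workload, keep it only for the detailed follow-up dataset or the interviews. There, reconcile fewer than three with more than three so that exactly three is covered, and say when and by whom conditions are counted.

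The cost is a revised criterion and slightly more data entry for patients with several conditions.
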